### Randomization to treatment groups

The randomization sequence will be computer-generated, stratified by nurse and blocked in groups of two. Study nurses will call the research units to give patient identification numbers and will be told the randomly assigned patient allocations. After this, participants in the intervention group will be scheduled for their first intervention visits.

The outcome assessors, data analyst, and physician will be blinded to patient allocation. To evaluate the effectiveness of blinding, these individuals will be asked to choose the arm to which they believed each patient was assigned (possible answers: intervention, usual care, or unknown). If they answered "intervention" or "usual care", they were asked to indicate what led to that belief.

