## Methods and Design

### Overview

Patients in a primary-care setting who have had low adherence to AHT, as assessed by the Morisky-Green or Haynes-Sackett tests, and elevated BP will be inform and ask to sign informed consent, those patients that agree to participate will be randomized equally to a "multifactorial intervention" group or a control group (which continued the usual care) (Figure 1). Participants in the intervention arm will receive three intervention sessions during a 9-month period. The intervention will be provided by study nurses who will have received special training for administration of motivational interviewing and in the implementation of the study protocol.

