### Training

The intervention nurses will attend a 16-h motivational interview training program to teach the theoretical underpinnings, principles, and "spirit" of motivational intervention and practical exercises (to be supervised by co-investigators [name] and [name]). This training program will include a thorough discussion of the study protocol and will instruct nurses to use terms consistently when recording the findings and documenting treatments on the intervention visitation documents. There will also be hands-on training sessions to ensure that the intervention nurses are comfortable with the protocol and the types of questions that participants may ask. The intervention nurses will also practice completing intervention forms and providing suggestions for self-care.

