### Statistical Issues

#### Sample size, clinical significance, statistical significance

We want to ensure that our clinical trial has adequate statistical power to detect a clinically significant difference of at least 6 mmHg at 1 year in systolic BP between groups with a two-tailed significance level of 0.05. Assuming a standard deviation of 15 mmHg and a 20% loss to follow-up, we would need to randomize 110 participants per group. We expect a 15% "contamination" of the control group (see below), yielding a 1.41 contamination effect [26]. Thus, the final target sample size is 320 patients.

The effectiveness of the intervention will be assessed by a clinically significant reduction in BP, cardiovascular mortality models shows an estimated 5-yr risk reduction of cardiovascular disease of 15-20% by a reduction of 5 mmHg in systolic blood pressure [27,28]. We have estimated that a difference of at least 10 mmHg at 1-yr is necessary to detect a clinically significant difference of at least 5 mm Hg at 5-yr.

Intervention will be provided to a group of participants by a single nurse, so we will consider the cluster effect during statistical analysis.

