An analysis of direct costs and outcomes for patients in both groups will be conducted by a nurse blinded to patient allocation. Clinical record review and detailed self-reported data on costs of healthcare utilization, clinical tests, and medication will be considered. All resources utilized will be multiplied by the appropriate cost using nationally applicable cost data. The cost of resource utilization (primary care visits, hospital admissions, clinical testing) will be estimated using the healthcare costs published in the *National Official Journal of Spain *or *Regional Officials Journal*. Costs of all AHTs will be calculated using prices published in the catalogue of pharmaceutical compounds by the Spanish Board of Pharmacists. Intervention costs will also consider the time needed to train nurses and the time of each intervention visit.

The primary health outcome for the cost analyses is BP reduction, which will be calculated using direct costs. The measure of "relative value for money" from the intervention is the incremental cost-effectiveness ratio calculated from the additional cost for a benefit of 1 mmHg reduction.

Analysis of costs may require variable transformation, but can be modeled using multivariate linear regression without a baseline value for costs because this value will be unknown. We will adjust for age, sex, and comorbidities that may affect cost. We recognize that we will have low statistical power to detect even moderate cost differences between the two groups.

Each nurse will provide intervention to a group of patients, so we will also measure the effect of individual nurses on outcome by multilevel analysis to determine if there is a significant variation across nurses that cannot be explained by random variation, also we will establish a number maximum of 10 patients per nurse to minimize this effect.

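### Fixed blocks of two within each nurse let the unblinded nurse who phones in patients know up to half of the allocations before the call

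*Protocol article*

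**What the plan says.** Under Randomization to treatment groups, the protocol article fixes both the stratum and the block size: "The randomization sequence will be computer-generated, stratified by nurse and blocked in groups of two". The next sentence describes how an allocation is obtained: "Study nurses will call the research units to give patient identification numbers and will be told the randomly assigned patient allocations". Allocation is 1:1 (Overview): "those patients that agree to participate will be randomized equally".

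The blinded roles are listed: "The outcome assessors, data analyst, and physician will be blinded to patient allocation". The study nurse is not among them and could not be, because of her task (Overview): "The intervention will be provided by study nurses who will have received special training".

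Two further statements bear on what a nurse can know. On training: "This training program will include a thorough discussion of the study protocol". On stratum size (Statistical Analysis): "we will establish a number maximum of 10 patients per nurse to minimize this effect". Nothing in the article says that the block size is varied or kept from the nurses, or that a nurse's patients are all registered before any of their arms is released.

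**The concern.** A central telephone call conceals an allocation only if the caller cannot work it out from earlier ones. Here the stratum is a single nurse, that nurse learns each arm as it is assigned, and the block holds one patient per arm. Once the first arm of a pair is known, the second is known too. A nurse who was never told the block size would still see up to five complementary pairs among her ten patients.

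If the person who knows the next arm has any say in which consenting patient is put forward, or when, the arms can differ at entry in ways related to 12-month systolic blood pressure. Blinded measurement at 12 months does not change who entered which arm, and intention-to-treat analysis keeps the groups as they were formed. Adjustment can help only for what is measured; motivation to take tablets, for example, is not among the measures in Table 1.

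**Working it through.** The article gives no figure for predictability, so there is none to reproduce.

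**Inputs from the article**
- Block size 2, stratum = nurse, ratio 1:1 (Randomization to treatment groups; Overview).
- At most 10 patients per nurse (Statistical Analysis).
- 320 patients, SD 15 mmHg, target difference 6 mmHg, 20% loss, two-sided 0.05 (sample size section).

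**Step 1. Allocations known with certainty.** In complete fixed blocks of size 2b, the share determined by earlier allocations in the block is 1/(b + 1).
- Block of 2 (b = 1): 1/2 = 50%. Of 320 patients, 160 if every pair is complete; of a nurse's ten, up to five.
- Block of 4 (b = 2): 1/3 = 33.3%.
- Block of 6 (b = 3): 1/4 = 25.0%.

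**Step 2. Correct guesses.** The nurse guesses the arm that is behind so far and tosses a coin when the arms are level. For a block of 2, the first guess is right half the time and the second always: (0.5 + 1)/2 = 75%. Enumeration gives 70.8% for complete blocks of 4 and 68.3% for complete blocks of 6.

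**Step 3. Undisclosed, randomly varying sizes, ten patients per nurse.** Simulation with the same guessing rule gives about 68% (sizes 4 and 6) and 69% (sizes 2, 4 and 6). A nurse who does not know the possible sizes can be certain of almost nothing. If the set of sizes leaked, exact enumeration over ten patients gives 6% certain for 4 and 6, and 3% for 2, 4 and 6.

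**Step 4. Illustrative bias.** The shift g is an assumption; the article gives no such figure. Suppose every second patient is steered so that expected 12-month systolic pressure moves by g mmHg, in opposite directions according to the known arm. Half of each arm is affected, so each arm mean moves by g/2 and the difference moves by g/2 + g/2 = g.

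Analysed per arm: 160 x 0.8 = 128. Standard error: 15 x sqrt(2/128) = 1.875 mmHg. Two-sided type I error = 1 - Φ(1.96 - g/1.875) + Φ(-1.96 - g/1.875).

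| g (mmHg) | Bias (mmHg) | Share of 6 mmHg target | Type I error |
|---|---|---|---|
| 0 | 0 | 0 | 0.050 |
| 1 | 1 | 1/6 | 0.083 |
| 2 | 2 | 1/3 | 0.187 |
| 3 | 3 | 1/2 | 0.360 |

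**Step 5. What varying blocks leave.** If nurses acted on guesses as readily as on certainties, the bias would be 2g(2p - 1), where p is the correct-guess rate.
- p = 0.75: 2g x 0.50 = g, as in step 4.
- p = 0.68: 2g x 0.36 = 0.72g.
- p = 0.69: 2g x 0.38 = 0.76g.

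In that worst case about three quarters of the bias remains. If nurses act only when certain, nearly all of it goes.

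**The case against.** The strongest reply is that predictability does harm only if someone can act on it, and the article does not show that the nurse can. It says that she telephones with an identification number; who screens and obtains consent is left in the passive. The article also limits discretion. Consent comes before randomisation. Eligibility rests on blood pressure thresholds and named adherence tests. Table 1 lists blood pressure for inclusion at two visits a month apart. Eligible patients who decline are counted. All participants test as low adherers, which narrows the range over which they could be selected.

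Much of this stands. A reader might infer that the nurse recruits and picks patients; the article does not say so. Nor do these limits close the gap. They do not stop whoever telephones from ordering or delaying consented patients, and no enroller unaware of earlier arms is named.

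A reader might also infer that concealment fails altogether. It does not: the call still conceals the first allocation of every pair. The count of 160 is an upper bound that needs complete pairs and nurses who know or have worked out the scheme.

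Finally, it could be said that a condensed article leaves such detail to the full protocol. That would answer a silence, but here the block size, the stratum and the unblinded caller are all stated.

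**Conclusion.** The point holds as a weakness in a stated rule. With fixed blocks of two inside a one-nurse stratum, the second allocation of each complete pair is known to the unblinded nurse before she calls: up to 160 of 320, with 75% of arms guessable. That part is arithmetic. It assumes only that the nurse knows the block size or infers it from her own patients.

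That selection bias will follow is not established. It depends on an enrolment process that the article does not describe, so the supported statement is that selection at entry is possible and would not be corrected by blinded assessment or intention-to-treat analysis. The 1 to 3 mmHg range is a scenario in which every nurse steers every known slot in the same direction. It should not be read as an estimate of the bias in this trial. The change is still worth making, because it costs little and a bias at entry cannot be reliably repaired afterwards.

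**What to change.** Delete the fixed block size of two. For all remaining allocations, use randomly varying block sizes (for example 4 and 6), generated and held at the research unit and not disclosed to nurses. Keep the telephone allocation.

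This removes nearly all certain allocations but leaves about 68-69% guessable while the stratum is a single nurse. Either of two further steps would reduce that:
- stratify above the nurse, for example by centre, with undisclosed varying blocks. This helps only where a centre has more than one study nurse, which the article does not state; or
- have all of a nurse's available patients consented and registered, in a fixed order, before any of their allocations is released.

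The article should also state who screens and obtains consent, and whether that person knows earlier allocations.

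Cost: a new list. With blocks of at most six within nurse, imbalance can reach three patients for a nurse. Across at least 320/10 = 32 nurses this is minor, and the planned multilevel analysis by nurse can handle it. Centre-level strata would allow larger imbalance within a nurse, and batch registration would delay the first patients in each batch.

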### Multifactorial Intervention

The intervention consists of five components that will be delivered during three interventional visits of about 30 min each. Use of a detailed intervention protocol and comprehensive motivational interview training is intended to increase the effectiveness of interventions. The study nurses will carefully document each component of the multifactorial intervention that they perform by use of specially designed intervention visitation documents and will register the time and the duration of each component of the intervention.

The five components of the intervention are:

1. ***Motivational interview: ***This will be based on the Health Belief Model [24] and the Prochaska and DiClemente stage of change [25], and will try to resolve ambivalences that patients have regarding medication and explore perceptions that patients have about their ability to control events (locus of control).

2. ***Pillbox Reminder: ***A pillbox organizer with seven compartments will be given to the patients. They will self-fill it with one pill for each day of the week. Use of the pillbox will be explained to patients in the intervention group.

3. ***Family Support: ***Patients will designate one person in their household who will be responsible for reminding and monitoring medication intake. The designated person must accept responsibility of reminding the patient to take medication and of supervising pill intake. If a patient lives alone or does not wish to involve a family member or carer, they do not need to designate anybody. Thus, this part of the intervention is not mandatory.

4. ***BP measurements and AHT reminder forms: ***Twelve forms (one per month) and a table will be completed by the patient and nurse and used to record the date and hour of all BP readings (including gaps). AHT dosage and a telephone contact number will also be recorded on each form. This information will be frequently updated. The forms will be provided to patients and nurses at visit 0, and patients will be asked to bring them to all subsequent visits.

5. ***Simplification of dosing regimens: ***AHT dosage will be recorded at visit 0, and pharmacists will simplify the dosing regimen when possible at subsequent visits.

Visit 1 (first month, 40 min total): motivational interviewing (25 min), pill reminder (5 min), self-recording of BP (5 min), family support, when possible (5 min).

Visit 2 (third month, 35 min total): motivational interview (25 min), simplification of dosing regimen, if possible, check of self-recording BP (5 min), family support, when possible (5 min).

Visit 3 (ninth month, 35 min total): motivational interview (25 min), check self-recording BP (5 min), and family support, when possible (5 min).

### Control group

Patients randomized to the control group will not receive any changes in their care. However, they will be contacted at baseline and at the 12th month and asked to complete the same outcome measures as the intervention group.

### Training

The intervention nurses will attend a 16-h motivational interview training program to teach the theoretical underpinnings, principles, and "spirit" of motivational intervention and practical exercises (to be supervised by co-investigators [name] and [name]). This training program will include a thorough discussion of the study protocol and will instruct nurses to use terms consistently when recording the findings and documenting treatments on the intervention visitation documents. There will also be hands-on training sessions to ensure that the intervention nurses are comfortable with the protocol and the types of questions that participants may ask. The intervention nurses will also practice completing intervention forms and providing suggestions for self-care.

### Assessment of outcomes

#### Primary outcome measure

The primary outcome measure is systolic BP at 12 months. BP will be measured according to ESH/ESC guidelines. Patients (instructed to not eat or smoke for 30 min) will be seated quietly, with their backs supported and feet on the floor for 5 minutes. Then, using an appropriately sized cuff, the bared arm will be supported, and an oscillometric BP machine with a printer will be used for three measurements. The nurse (blinded to patient allocation) will write all three BP measurements on the final visit form.

#### Secondary outcome measures

Secondary outcomes are diastolic BP, proportion of participants with adequate BP control at 12 months, total direct cost, absolute and relative risk reduction, number of patients need to treat for benefit, and change in adherence at 12 months (measured by the Haynes-Sackett test).

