**Measurement:**

The primary outcome is systolic blood pressure. The secondary outcomes are diastolic blood pressure, proportion of patients with adequately controlled blood pressure, and total cost.

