**Figure 1 F1:**
[figure not shown]
**Study design Flow-chart**.

Table 1 summarizes the measures and variables according to the timeline. Participants will be studied for 1 year following randomization. Primary and secondary outcomes will be assessed by an external nurse who will be blinded to treatment assignment after 12 months. The primary outcome will be systolic BP. Secondary outcomes will include diastolic BP, direct costs, and the number of patients who required treatment to yield one patient with normalized BP.

**Table 1 T1:** Measures, variables and timeline

VISIT	-1	0	1	2	3	4
Time (months)	-1	0	1	3	9	12
Blood pressure measurement inclusion criteria	X	X				
Morisky-Green and Haynes-Sackett tests	X					
Inclusion and exclusion criteria	X					
Comorbidities		X				
Blinded blood pressure measurement						X
Medication use						X
Adverse effects to medication		X				X
Medical consultation, cardiovascular events and hospital admission.						X
Checklist and time duration of intervention components (Intervention group)			X	X	X	
Motivational interview (Intervention group)			X	X	X	
Pill reminder (Intervention group)			X			
Family support (Intervention group)			X	X	X	
Blood pressure self-recording (Intervention group)			X	X	X	
Simplification of dosing regimens (Intervention group)			X			

Information bias will be minimized by use of a design that provides the maximum possible level of masking for studies of non-pharmacological intervention. In particular, the outcome assessor, data analyst, and physician will all be blinded to patient allocation. Misclassification, if any, is expected to be non-differential. Quality control will include recording of patient adherence to interventions, inclusion and follow-up monitoring, and quality supervision of data entry. We will perform an intention-to-treat analysis of the data; that is, the analysis will be by randomized assignment regardless of participation in intervention sessions.

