### Inclusion and exclusion criteria

The inclusion criteria are: age 18-75 years; poor BP control based on European Societies of Hypertension and Cardiology (ESH/ESC) guidelines (< 140/90 mmHg or < 130/80 mmHg in patients with diabetes or renal failure); and low adherence to medication as assessed by the Morisky-Green or Haynes-Sackett tests. The exclusion criteria are: presence of non-essential hypertension; treatment by hemodialysis; and institutionalization or terminal illness.

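### Table 1 schedules the adherence tests at visit -1 only, which contradicts the secondary outcome of 12-month change in adherence by the Haynes-Sackett test

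*Protocol article*

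**What the plan says.** The protocol article (section Secondary outcome measures) fixes the time and the instrument for this outcome: "change in adherence at 12 months (measured by the Haynes-Sackett test").

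Table 1 (Methods and Design, Overview) has a row labelled "Morisky-Green and Haynes-Sackett tests". Its only mark is in the first column, visit -1.

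Two general statements bear on month 12. The Overview says: "Primary and secondary outcomes will be assessed by an external nurse who will be blinded to treatment assignment after 12 months". The Control group section says of control patients that "they will be contacted at baseline and at the 12th month and asked to complete the same outcome measures as the intervention group". Neither names an adherence test.

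The other two lists of secondary outcomes leave adherence out. The abstract has: "The secondary outcomes are diastolic blood pressure, proportion of patients with adequately controlled blood pressure, and total cost". The Overview has: "Secondary outcomes will include diastolic BP, direct costs, and the number of patients who required treatment to yield one patient with normalized BP".

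For entry, either test is enough: "low adherence to medication as assessed by the Morisky-Green or Haynes-Sackett tests".

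**The concern.** A declared outcome cannot be derived from the schedule as printed. Sites usually work from the visit table, and a nurse who follows Table 1 at month 12 would not give the Haynes-Sackett test. An answer not taken then cannot be reconstructed from records.

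The value matters for interpretation. Better adherence is what the intervention aims at, and this is the only listed outcome that measures it directly. The Limitations section names another route to lower blood pressure, namely physicians changing medication, and admits that physicians may learn the allocation. Without a 12-month adherence value, a blood pressure difference is harder to attribute to adherence. A null result would also leave open whether adherence failed to change or changed without lowering blood pressure.

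A smaller matter goes with it. Patients may enter on Morisky-Green alone, while the outcome uses Haynes-Sackett alone.

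**Working it through.** No figure in the plan is at issue, so the check sets the places side by side.

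1. **The adherence row in Table 1.** The row has six visit cells (visits -1, 0, 1, 2, 3 and 4). One is marked, visit -1; the other five are blank. Adherence tests at visit 4: none.

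2. **The visit 4 column in Table 1.** Four rows are marked: blinded blood pressure, medication use, adverse effects, and the row "Medical consultation, cardiovascular events and hospital admission". None is an adherence test. The medication use row does not fill the gap, because the outcome is tied to a named test.

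3. **Is the blank a reading error?** This is unlikely. Neighbouring rows keep their alignment, and a repeated item, adverse effects, carries marks at both visit 0 and visit 4.

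4. **What the outcome needs.** Change = value at month 12 minus (or compared with) value at baseline. Table 1 supplies the baseline, since both tests are given at visit -1. It does not supply the month-12 value. Time points needed: 2; time points scheduled: 1.

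5. **What the text adds.** The outcome definition names month 12 and the Haynes-Sackett test. The Overview has secondary outcomes assessed by the blinded nurse, and the Control group section gives controls the same outcome measures at month 12. Read together, these point to an intended test at visit 4 that the table omits.

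6. **Entry test against outcome test.** A patient who qualifies on Morisky-Green alone is, by that fact, not a low adherer on Haynes-Sackett at visit -1. If Haynes-Sackett is scored yes/no, that patient cannot improve on it. The article gives neither the scoring nor the share of such patients, so the effect on the outcome cannot be sized from the document.

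**The case against.** The strongest reply is that the text already settles the matter. The outcome definition gives time and instrument, two further statements put outcome assessment at month 12 in both arms, and Table 1 is introduced only as a summary. The table also appears incomplete elsewhere: the Adverse Events section has participants asked at each visit, while Table 1 marks adverse effects at visits 0 and 4 only. On this view a cell was left blank by oversight.

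Most of this stands. A reader might infer from Table 1 that the outcome cannot be obtained, or that none of the 320 patients will have a 12-month value. The document does not support that, because three places in the text point to a month-12 assessment. What remains is that the one itemised schedule disagrees with the outcome definition. Nor does condensation for a journal explain it, since the article prints both the outcome and the timeline.

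A reader might also infer that the single-test outcome is invalid, or that it dilutes the effect by a calculable amount. Neither follows. Using one named test is legitimate even when entry allows either of two. Every patient is scheduled for a baseline Haynes-Sackett result. Because the comparison is randomised, a ceiling does not bias it between arms and at most costs sensitivity. Any dilution figure would need an assumed share of patients already adherent on Haynes-Sackett, yes/no scoring, and no difference between arms among those patients. The last is doubtful, since the intervention could still prevent worsening in that group.

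Finally, the article plans no mediation analysis, so the adherence result would help interpretation but is not a formal part of the primary question.

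**Conclusion.** The contradiction between Table 1 and the secondary outcome definition is real and should be corrected. Its consequence is conditional: if sites follow Table 1 literally, the 12-month Haynes-Sackett value is not collected and the change in adherence cannot be computed; if they follow the text, it is.

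The damage is confined to one secondary outcome, which two of the article's three lists of secondary outcomes do not mention. Systolic blood pressure at 12 months is scheduled at visit 4, and neither the sample size nor the primary analysis uses adherence. Severity is low to moderate. The correction is still worth making before month-12 visits begin, because the loss could not be repaired afterwards.

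The mismatch between entry test and outcome test is a side remark. It depends on yes/no scoring and on a share of patients that the article does not report.

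**What to change.** - In Table 1, mark the Haynes-Sackett test at visit 4 for both arms, and state that the blinded external nurse gives it.
- Keep Haynes-Sackett as the prespecified outcome. Compare the arms at 12 months, using the visit -1 result as baseline.
- Optionally, repeat Morisky-Green at the same visit and report it as a supportive measure, because some patients may have entered on that test alone. A composite of the two tests should not replace the prespecified outcome; that would redefine it and is not needed to remove the contradiction.
- When the table is corrected, bring the secondary outcome lists in the abstract and the Overview into line with the section on secondary outcome measures.

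The cost is one entry in the schedule, or two with the optional test, and a few questionnaire minutes at a visit that already takes place. No change to the sample size or the primary analysis follows.
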